#### 3.5.5.2 Statistical Methods for Assessment of HPV type Replacement

Possible HPV type replacement will be studied in the cohort of adult women in Colombia. While HPV type-specific, population-based data are not available in Colombia, type replacement can be assessed by describing the proportion of non-vaccine HPV types that produce high grade lesions as a percent of total biopsies obtained within the region where Protocol 019 was conducted. The incidence of CIN 2+ due to non-vaccine types in Cohorts 1 and 2 will be descriptively compared to the incidence of HPV type-specific CIN 2+ from similarly aged women in the cohort study performed by [name] and colleagues [4] in Bogota, Colombia. CIN 2+ HPV types that will be descriptively studied are the 10 non-vaccine types tested in the base study, HPV 31/33/35/39/45/51/52/56/58/59.

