## 1.2 Indication for Long term Follow-Up

HPV type-specific effectiveness endpoints will be collected by active surveillance of Pap abnormalities, biopsy and EEC specimens, and definitive therapy specimens using the clinic and investigators in Bogota, Colombia with all specimens tested as in Protocol 019 base study.

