## 2.4 Study Design and Duration

### 2.4.1 Summary of Study Design

Approximately 1,600 healthy women, previously enrolled in Protocol 019 (the base study) and/or Protocol 019-10 in Colombia, will sign an informed consent prior to initiation of any study procedure. The women were 24 to 45 years of age when enrolled in the base study. During the base study at Day 1, subjects were stratified by age into 2 groups: those 24 to 34 years of age and those 35 to 45 years of age. Stratification accomplished balanced allocation within each stratum. In Colombia, approximately 800 subjects were vaccinated with GARDASIL™ during the base study at Day 1 and approximately 800 base study placebo recipients were vaccinated with GARDASIL™ at the end of the base study at approximately Year 5 in accordance with Protocol 019-10.

Safety data following administration of GARDASIL™ were collected on all study subjects within the context of Protocol 019 base study and Protocol 019-10 extension. Investigator-reported serious adverse event data as well as pregnancy outcomes will be collected within the context of this study (Protocol 019-20). The response of the immune system to the vaccine will be measured with a multiplex, competitive Luminex Immunoassay (anti-HPV 6, 11, 16, and 18 cLIA) and other serological assays. The PCR assays used to identify effectiveness endpoints are described in Section 3.3.4. The composition and operation of the blinded Independent Pathology Panel as well as the Panels roles and responsibilities are described in Section 3.3.7.2. The pathology endpoints will be determined by the Independent Pathology Panel, as in the base study.

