| Cohort 2 | 5-year incidence (Dose 1 to Year 10)  4-year incidence (Years 6 to 10) | vs.  vs. | N/A  4-year incidence‡ in Cohort 2║; 4-year incidence‡ in Cohort 1;  4-year incidence‡ in the GARDASIL™ group. |
| † Cumulative incidence from Day 1 to Year 2; and also cumulative incidence from Year 2 to Year 4.  ‡ Cumulative incidence from Day 1 to Year 4.  § Subjects from Colombia randomized to the GARDASIL™ group.  ║ Subjects from Colombia randomized to the placebo group.  ¶ Cumulative incidence from Day 1 to Year 3.  # Cumulative incidence from Years 4 to 8.  LTFU = Long term follow-up; N/A = Not available. There is no corresponding incidence during the base study. | | | |

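### The percent-of-biopsies measure cannot separate type replacement from vaccine success, and the incidence measure omits the trial's own Colombian base-study arms

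*Protocol*

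**What the plan says.** Section 3.5.5.2 of the protocol names two measures of type replacement.

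- **A share.** "type replacement can be assessed by describing the proportion of non-vaccine HPV types that produce high grade lesions as a percent of total biopsies". The biopsies are those from the region where Protocol 019 ran. No count is given.
- **An incidence.** "The incidence of CIN 2+ due to non-vaccine types in Cohorts 1 and 2 will be descriptively compared to the incidence" of type-specific CIN 2+ "from similarly aged women in the cohort study performed by" an outside group in Bogota. No base-study comparator is named.

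The same section states that "CIN 2+ HPV types that will be descriptively studied are the 10 non-vaccine types tested in the base study", so base-study typing of these types exists. Section 1.2 describes follow-up "with all specimens tested as in Protocol 019 base study", and Section 3.3.7.2 keeps the base study's Pathology Panel.

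For effectiveness the protocol does use internal references. Table 3-4 sets the follow-up incidences beside the base-study arms, including the group footnoted as "Subjects from Colombia randomized to the placebo group". That table and the text of Section 3.5.5.1 concern endpoints related to HPV 6/11/16/18. Section 3.5 says that no separate SAP will be issued, so the choice is made here.

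**The concern.** Replacement means that disease from non-vaccine types becomes more frequent. A share of biopsies answers a different question, because it depends on vaccine-type lesions and on how many biopsies are taken as well as on non-vaccine lesions. An effective vaccine can therefore move the share with no change in non-vaccine disease.

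The incidence measure is free of that artefact. Its weakness is that the only named comparator is outside the trial, while arms recruited from the same population and assessed with the same typing and Panel are left out. The objective in Section 2.1.3 could then be reported from one measure that is ambiguous by construction and another whose comparability cannot be checked from the protocol.

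**Working it through.** Section 3.5.5.2 states no figure, so there is none to reproduce.

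**Inputs** (Table 3-6, full analysis set, Colombia, Year 4, CIN 2/3 or worse)

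| | GARDASIL | Placebo |
|---|---|---|
| Any HPV type | 24 | 22 |
| HPV 16/18-related | 10 | 13 |
| Difference (non-16/18) | 14 | 9 |

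The table counts women, and I take one lesion and one biopsy per case. Total biopsies B is not in the protocol and is assumed. I read the denominator as the study's own biopsies.

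**1. The share with no replacement.** Hold non-vaccine lesions at N = 9 and remove V = 13 lesions. The share goes from N/B to N/(B − V).

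| B (assumed) | Before | After |
|---|---|---|
| 50 | 9/50 = 18.0% | 9/37 = 24.3% |
| 100 | 9/100 = 9.0% | 9/87 = 10.3% |
| 200 | 9/200 = 4.5% | 9/187 = 4.8% |
| 400 | 9/400 = 2.25% | 9/387 = 2.33% |

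The extreme is B = 22, where only CIN 2+ lesions are counted: 9/22 = 41% becomes 9/9 = 100%.

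Total biopsies also include lower-grade and external lesions. Table 3-6 gives 38 Colombian placebo women with vaccine-type CIN or external genital lesions by Year 4. Removing 38 instead of 13 (one biopsy each, none overlapping the nine) gives 9/62 = 14.5% at B = 100 and 9/162 = 5.6% at B = 200.

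**2. Mixed-type lesions.** Section 2.5.3 counts a lesion when the relevant non-vaccine type is detected, whether or not a vaccine type is also present. If m of the 13 removed lesions were also counted as non-vaccine cases, the share goes from (9 + m)/B to 9/(B − 13). It falls when m > 9 × 13/(B − 13). At B = 100 the bound is 117/87 = 1.3, so two mixed lesions suffice: 11.0% to 10.3%. At B = 200 it is 117/187 = 0.6, so one suffices: 5.0% to 4.8%. The share can therefore move either way with no replacement.

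**3. What the internal comparison can show.** With an assumed 800 per arm, non-16/18 CIN 2/3+ by Year 4 is 14/800 = 1.75% against 9/800 = 1.12%, a risk ratio of 14/9 = 1.56. The standard error of its log is √(1/14 − 1/800 + 1/9 − 1/800) = 0.424, giving a 95% CI of 0.68 to 3.57 (Fisher p = 0.40). Subtracting the life-table estimates gives 3.13 − 1.32 = 1.81% against 3.06 − 1.76 = 1.30%. With 800 per arm and a 1.12% reference rate, power is about 42% for a risk ratio of 2 and 86% for 3. The comparison is feasible but imprecise.

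**The case against.** **An incidence measure is already planned.** This stands. Sections 2.1.3 and 2.5.3 define replacement by incidence, per subject and per type, and Section 3.5.5.2 carries this through for CIN 2+. The criticism of that measure is confined to its comparator.

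**The artefact is small on the stated denominator.** This also stands. A reader might infer that the share must rise whenever vaccine-type lesions fall, or that it would jump from 41% to 100%. The protocol supports neither. The rise needs a constant non-vaccine count, mixed lesions can undo it, and the large jump needs every biopsy to be CIN 2+. Biopsies are taken of each abnormal area and of suspected genital lesions (Sections 3.2.3.3.7.2 and 3.2.3.3.7.3), so the denominator is wider.

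**Base-study context is promised elsewhere.** Section 3.5.5 sets cohort incidences against base-study incidences without naming types, and Section 3.5.3 includes the replacement endpoints. But Section 2.7 ties this context to vaccine effectiveness, and Section 3.5.5.1 with Table 3-4 specifies it only for HPV 6/11/16/18. No commitment for replacement follows.

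**The outside cohort may be suitable.** Its screening, histology and typing methods are not described in the protocol, so nothing here shows that they differ. It is also chosen for similar age, which the placebo arm cannot offer for the later follow-up years.

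**The internal reference has its own bias.** This is right and shapes the fix. Under Section 2.7, women who were base-study cases are left out of the follow-up analysis of that endpoint, while the base-study full analysis set includes women infected at entry. An unaligned comparison could hide replacement.

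**Conclusion.** The point holds as a defect in how a descriptive objective is specified. The percent of biopsies should not be interpreted as replacement, because it mixes loss of vaccine-type lesions with change in non-vaccine lesions. The shift is modest on the literal denominator (9.0% to 10.3% at 100 biopsies, 4.5% to 4.8% at 200), grows as the denominator narrows towards CIN 2+ lesions, and has no fixed sign once mixed lesions are counted. These sizes rest on assumed biopsy totals and one lesion per case. The incidence measure is the right one, but it lacks an internal reference that the protocol already uses for effectiveness. No hypothesis test is affected.

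Two stronger inferences are not supported.

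- The GARDASIL share of 14/24 = 58% against 41% on placebo does not demonstrate the artefact. Had the remainder stayed at nine, the share would have been 9/19 = 47%. Most of the gap is the higher non-16/18 count.
- The base-study counts do not show that replacement has occurred. Over the whole base study, subtraction gives 38/1,910 against 21/1,907, a crude risk ratio of 1.81 (95% CI 1.06 to 3.07). But the full analysis set includes infections present at entry, the difference may retain HPV 6/11 lesions, and it misses women with both kinds of lesion.

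**What to change.** In Section 3.5.5.2:

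- Make the replacement measure the incidence of Panel-confirmed CIN 2+ positive for any, and for each, of the ten types. Use the life-table cumulative incidence of Section 3.5.5.1, supported by person-year rates with exact confidence intervals.
- Set it against the Colombian base-study placebo and GARDASIL arms over intervals of equal length, in the manner of Table 3-4.
- State the population and align it as far as the data allow, for example women naive to the relevant type at base-study Day 1 for Cohort 1. The serology in Section 3.3.3 covers only the four vaccine types, so for the other ten this depends on what base-study PCR results exist. For Cohort 2, where only the full analysis set is available, state the direction of the bias.
- Repeat the analysis excluding lesions also positive for HPV 6/11/16/18.
- Keep the outside cohort as supportive context. If the percent of biopsies is reported, define its denominator and say that it is not a measure of replacement.

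The cost is re-tabulation of data that the protocol indicates are held. The limits should be stated: the placebo reference ends when "approximately 800 base study placebo recipients were vaccinated with GARDASIL™ at the end of the base study at approximately Year 5", Table 3-6 runs only to Year 4, and the women were then younger and observed earlier. It is a descriptive reference with low precision, not a concurrent control.

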#### 3.5.5.3 Statistical Methods for Assessment of Immunogenicity

The procedure for estimating geometric mean titers (GMTs) as described in Section 3.3.2 of the V501-019 SAP will be used. GMTs and corresponding 95% confidence intervals of HPV (6, 11, 16, and 18) will be summarized for the time points indicated in Table 3-5.

Table 3-5

Summary of Time Points Post-Vaccine Dose 1 For Which HPV (6, 11, 16, and 18) Titers Will Be Available from the Base Study and LTFU Study

| Cohort | Time from Vaccine Dose 1 (in Months) | | | | | | | | |
| --- | --- | --- | --- | --- | --- | --- | --- | --- | --- |
| 7 | 12 | 24 | 36 | 48 | 60 | 72 | 96 | 120 |
| GARDASIL™ Group (Base study) † | + | + | + | + | + |  |  |  |  |
| Cohort 1 (LTFU study)† | + | + | + | + | + |  | + | + | + |
| Cohort 2 (LTFU study) |  | + |  | + |  | + |  |  |  |
| + indicates that HPV (6, 11, 16, and 18) titers will be available corresponding to the indicated time point in the indicated cohort at the end of the LTFU study.  † Cohort 1 includes subjects enrolled and vaccinated with GARDASIL™ on Day 1 in the base study who continued into LTFU.  LTFU = Long term follow-up. | | | | | | | | | |

### 3.5.6 Multiplicity

No hypothesis will be tested in this LTFU study. Therefore, multiplicity adjustment does not apply to this study.

### 3.5.7 Power and Sample Size

As stated in Section 2.7, the sample size for the effectiveness and immunogenicity components of the LTFU study is fixed by the number of Protocol 019 base study participants from Colombia who are eligible and willing to participate in this LTFU study. The expected number of cases that can potentially be observed during the LTFU study based on ~1,600 subjects, together with the number of cases observed in some endpoints during the base study, makes it difficult to statistically differentiate the incidences observed during the LTFU study with the comparator incidences identified in Table 3-4. As an example, Table 3-6 shows the incidences observed during the base study for some selected vaccine HPV type-related disease endpoints in the per-protocol efficacy and full analysis set populations. For the endpoint of HPV 16/18-related CIN 2/3 or worse in the per-protocol efficacy population, the 4-year cumulative incidence (based on life-table estimate) during the base study are as follows:

- 0% in Cohort 1 (i.e., Colombia subjects randomized to the GARDASIL™ group) (the asymptotic standard error of cumulative incidence based on life-table method is 0 due to zero cases observed, therefore, 95% CI of cumulative incidence is not estimable);
- 0.07% (95% CI: 0.01 to 0.47) in the GARDASIL™ group;
- 0.41% (95% CI: 0.19 to 0.92) in the placebo group;
- 0.47% (95% CI: 0.15 to 1.46) among Colombia subjects randomized to the placebo group (i.e., Cohort 2 subjects).

Thus, for the base study 4-year cumulative incidence of HPV 16/18-related CIN 2/3 or worse in the per-protocol efficacy population, the incidence in the GARDASIL™ group is not statistically differentiable from the incidence in the placebo group (either all placebo recipients or only placebo recipients from Colombia). Consequently, it will be difficult to statistically differentiate the 4-year cumulative incidence of HPV 16/18-related CIN 2/3 or worse in the per-protocol efficacy population in Cohort 1 during the LTFU study (either from Years 4 to 8 or Years 6 to 10) from the base study 4-year cumulative incidence in the placebo group (either all placebo recipients or only placebo recipients from Colombia).

Table 3-6

Life-Table Estimate of Cumulative Incidence of HPV 6/11/16/18-Related Disease Endpoints During the Base Study
(Per-Protocol Efficacy and Full Analysis Set Populations)

| Endpoint | Time from Vaccine Dose 1 | GARDASIL™  (N=1,910) | | | Placebo (N=1,907) | | |

|  | Year 3 | 3 | 0.39 | (0.13, 1.20) | 6 | 0.77 | (0.35, 1.71) |
|  | Year 4 | 3 | 0.39 | (0.13, 1.20) | 7 | 0.90 | (0.43, 1.89) |
| HPV 16/18-related CIN 2/3 or worse |  |  |  |  |  |  |  |
| All base study subjects | Year 2 | 17 | 0.94 | (0.58, 1.50) | 19 | 1.03 | (0.66, 1.61) |
|  | Year 3 | 21 | 1.17 | (0.76, 1.79) | 23 | 1.27 | (0.84, 1.90) |
|  | Year 4 | 21 | 1.17 | (0.76, 1.79) | 27 | 1.53 | (1.08, 2.30) |
| Colombia cohort | Year 2 | 7 | 0.90 | (0.43, 1.88) | 8 | 1.02 | (0.51, 2.02) |
|  | Year 3 | 10 | 1.32 | (0.71, 2.43) | 9 | 1.16 | (0.60, 2.20) |
|  | Year 4 | 10 | 1.32 | (0.71, 2.43) | 13 | 1.76 | (1.08, 3.28) |
|  |  |  |  |  |  |  |  |
| CIN 2/3 or worse Due to Any HPV Type |  |  |  |  |  |  |  |
| All base study subjects | Year 2 | 48 | 2.63 | (1.98, 3.47) | 34 | 1.86 | (1.33, 2.58) |
|  | Year 3 | 55 | 3.04 | (2.34, 3.93) | 38 | 2.09 | (1.52, 2.86) |
|  | Year 4 | 59 | 3.28 | (2.59, 4.29) | 48 | 2.75 | (2.15, 3.79) |
| Colombia cohort | Year 2 | 20 | 2.58 | (1.67, 3.96) | 13 | 1.67 | (0.97, 2.86) |
|  | Year 3 | 23 | 2.99 | (1.99, 4.46) | 15 | 1.94 | (1.18, 3.21) |
|  | Year 4 | 24 | 3.13 | (2.15, 4.77) | 22 | 3.06 | (2.13, 4.98) |
| N = Number of subjects randomized to the respective vaccination group who received at least 1 injection.  CI = Confidence interval; CIN = Cervical intraepithelial neoplasia; EGL = External genital lesions; HPV = Human papillomavirus. | | | | | | | |

## 3.6 Data Management

Information regarding Data Management procedures for this protocol will be provided by the SPONSOR.

### 3.6.1 Study Documentation and Records Retention

Government agency regulations and directives require that all study documentation pertaining to the conduct of a clinical trial must be retained by the investigator. They shall be retained until at least 2 years after the last approval of a marketing application in an International Conference on Harmonisation (ICH) region, or at least 2 years have elapsed since the formal discontinuation of clinical development of the investigational product. These documents should be retained for a longer period, however, if required by the applicable regulatory requirements or by an agreement with the sponsor. The SPONSOR will notify the investigator in writing when retention is no longer necessary.

### 3.6.2 Laboratory Results

All assay results will be entered into the MRL clinical database.

## 3.7 Biological Specimens

Information regarding biological specimens for this protocol will be provided by the SPONSOR.

### 3.7.1 Shipment

Properly labeled specimens will be shipped according to instructions summarized in the SPONSOR’s central laboratory manual. Inventory forms, tubes for freezing/shipping specimens, and shipping containers will be provided by the SPONSOR’s central laboratory.

# 4. ADMINISTRATIVE AND REGULATORY DETAILS

## 4.1 Confidentiality

### 4.1.1 Confidentiality of Data

For Studies Conducted Under the U.S. IND

Particular attention is drawn to the regulations promulgated by the Food and Drug Administration under the Freedom of Information Act providing, in part, that information furnished to clinical investigators and Institutional Review Boards will be kept confidential by the Food and Drug Administration only if maintained in confidence by the clinical investigator and Institutional Review Board.

For All Studies

By signing this protocol, the investigator affirms to the SPONSOR that information furnished to the investigator by the SPONSOR will be maintained in confidence and such information will be divulged to the Institutional Review Board, Ethics Review Committee, or similar or expert committee; affiliated institution; and employees only under an appropriate understanding of confidentiality with such board or committee, affiliated institution and employees. Data generated by this study will be considered confidential by the investigator, except to the extent that it is included in a publication as provided in the Publications section of this protocol.

### 4.1.2 Confidentiality of Subject/Patient Records

For All Studies

By signing this protocol, the investigator agrees that the SPONSOR (or SPONSOR representative), Institutional Review Board/Independent Ethics Committee (IRB/IEC), or Regulatory Agency representatives may consult and/or copy study documents in order to verify worksheet/case report form data. By signing the consent form, the subject/patient agrees to this process. If study documents will be photocopied during the process of verifying worksheet/case report form information, the subject/patient will be identified by unique code only; full names/initials will be masked prior to transmission to the SPONSOR.

For Studies Conducted Under the U.S. IND

By signing this protocol, the investigator agrees to treat all patient data used and disclosed in connection with this study in accordance with all applicable privacy laws, rules and regulations, including all applicable provisions of the Health Insurance Portability and Accountability Act and its implementing regulations, as amended from time to time. (“HIPAA”).

### 4.1.3 Confidentiality of Investigator Information

For All Studies

By signing this protocol, the investigator recognizes that certain personal identifying information with respect to the investigator, and all subinvestigators and study site personnel, may be used and disclosed for study management purposes, as part of a regulatory submissions, and as required by law. This information may include:

- name, address, telephone number, and email address;
- hospital or clinic address and telephone number;
- curriculum vitae or other summary of qualifications and credentials; and
- other professional documentation.

Consistent with the purposes described above, this information may be transmitted to the SPONSOR, and subsidiaries, affiliates and agents of the SPONSOR, in your country and other countries, including countries that do not have laws protecting such information. Additionally, the investigator’s name and business contact information may be included when reporting certain serious adverse events to regulatory agencies or to other investigators. By signing this protocol, the investigator expressly consents to these uses and disclosures.

For Multicenter Studies

In order to facilitate contact between investigators, the SPONSOR may share an investigator’s name and contact information with other participating investigators upon request.

## 4.2 Compliance with Law, Audit, and Debarment

By signing this protocol, the investigator agrees to conduct the study in an efficient and diligent manner and in conformance with this protocol; generally accepted standards of Good Clinical Practice; and all applicable federal, state, and local laws, rules and regulations relating to the conduct of the clinical study.

The Code of Conduct, a collection of goals and considerations that govern the ethical and scientific conduct of clinical investigations sponsored by Merck Sharp & Dohme Corp., a subsidiary of Merck & Co., Inc., is attached.

The investigator also agrees to allow monitoring, audits, Institutional Review Board/Independent Ethics Committee review, and regulatory agency inspection of trial-related documents and procedures and provide for direct access to all study-related source data and documents.

The investigator agrees not to seek reimbursement from subjects/patients, their insurance providers, or from government programs for procedures included as part of the study reimbursed to the investigator by the SPONSOR.

The Investigator shall prepare and maintain complete and accurate study documentation in compliance with Good Clinical Practice standards and applicable federal, state, and local laws, rules and regulations; and, for each subject/patient participating in the study, provide all data, and upon completion or termination of the clinical study submit any other reports to the SPONSOR as required by this protocol or as otherwise required pursuant to any agreement with the SPONSOR.

Study documentation will be promptly and fully disclosed to the SPONSOR by the investigator upon request and also shall be made available at the investigator’s site upon request for inspection, copying, review, and audit at reasonable times by representatives of the SPONSOR or any regulatory agencies. The investigator agrees to promptly take any reasonable steps that are requested by the SPONSOR as a result of an audit to cure deficiencies in the study documentation and worksheets/case report forms.

International Conference of Harmonization Good Clinical Practice guidelines (Section 4.3.3) recommend that the investigator inform the subject’s primary physician about the subject’s participation in the trial if the subject has a primary physician and if the subject agrees to the primary physician being informed.

According to European legislation, a SPONSOR must designate a principal or coordinating investigator (CI) to review the report (summarizing the study results) and confirm that to the best of his/her knowledge the report accurately describes conduct and results of the study. The SPONSOR may consider one or more factors in the selection of the individual to serve as the CI (e.g., thorough understanding of clinical trial methods, appropriate enrollment of subject/patient cohort, timely achievement of study milestones, availability of the CI during the anticipated review process).

The investigator will promptly inform the SPONSOR of any regulatory agency inspection conducted for this study.

Persons debarred from conducting or working on clinical studies by any court or regulatory agency will not be allowed to conduct or work on this SPONSOR’s studies. The investigator will immediately disclose in writing to the SPONSOR if any person who is involved in conducting the study is debarred, or if any proceeding for debarment is pending or, to the best of the investigator’s knowledge, threatened.

In the event the SPONSOR prematurely terminates a particular trial site, the SPONSOR will promptly notify that site’s IRB/IEC.

